Systematic reviews and meta-analysis studies confirm the hypothesis that physical inactivity [18, 19], high sedentary behavior [20, 21], short and long sleep duration [22], and sleeping problems, such as insomnia [23, 24], are associated with greater chances of developing depression. However, the reverse direction of these associations may also occur, suggesting that individuals with depressive symptoms are more likely to be physically inactive or not meet physical activity recommendations [13, 15, 16, 19], to present high levels of sedentary behavior [13, 16], and to develop sleep disorders [14, 17], in compared to those without a diagnosis of this disease. As for clinical trials investigating these behaviors and depressive episodes, it is possible to see positive results, with physical activity providing antidepressant effects on the disease [19] and sleep bringing improvements in general mental health, depression, and other mental health problems, such as anxiety, stress, and rumination [14]. For sedentary behavior, what generally occurs is the development of interventions in which physically active participants are exposed to a reduction in the physical activities they usually do for, approximately, 1 week with the purpose of examining the effect of these changes on symptoms of mood, stress, and depression [25–27].

Furthermore, little is known about the long-term effects of these interventions. In addition to the heterogeneous data on monitoring and maintenance [28], there is a lack of studies regarding the remission of depression symptoms and the continuity of healthy behaviors [29]. Although short-term results can be achieved for both depressive symptoms [9, 11, 12] and 24-h movement behaviors [14, 19, 25], it is crucial to emphasize the significance of investigating these variables in the long term, months after the interventions have concluded. This approach is essential for filling critical gaps in understanding the enduring impacts of these interventions. Despite the benefits of a healthy lifestyle, individuals with depressive symptoms experience barriers such as the inherent symptomatology of the disease, leading to a lack of motivation and loss of interest [2], common factors for discontinuation of health promotion efforts across various contexts.

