### Sample size, randomization, and allocation concealment

The sample size was calculated using G*power 3.1.9.2 software, and was based on an ANOVA model for repeated measures with three time points and two groups. Parameters included an average effect size of 0.25, statistical power of 80%, and 5% significance level for two-tailed tests, reaching a value of 28 individuals. Anticipating a potential dropout rate of up to 50%, the number calculated was doubled, bringing the total sample size to 56 individuals. Eligible individuals were randomly assigned to either the control group (CG), instructed to maintain their usual activities, or the intervention group (IG), which actively participated in the program. To ensure numerical and participant characteristic balance between groups, randomization was stratified by sex, age, and PHQ-9 score, employing a 1:1 ratio. The randomization process was executed using the online platform randomizar.org by researchers not directly involved in the intervention. The allocation list was concealed from all study evaluators.

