### Assessments

The assessment of the variables of interest was carried out at three moments: (a) baseline pre-intervention (January 2023); (b) post-intervention, immediately following the conclusion of the program (May 2023); and (c) post-intervention, 6 months after the end of the intervention (follow-up evaluation, conducted in November 2023). Questionnaires were employed to measure the variables, and participants were required to respond in the presence of a previously trained researcher. To facilitate this process, specific dates and times were scheduled based on participants’ availability. Furthermore, during these assessment periods, participants used accelerometers to objectively measure their 24-h movement behaviors. In Fig. 1, it is possible to observe a schematic diagram with the time schedule of enrolment, interventions, and assessments.

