To verify the effect of the intervention on the primary outcome and secondary outcomes, per-protocol and intention-to-treat analyses will be conducted. The first one will take into account only IG participants who followed the activities until the last meeting, complied with the planned intervention protocol with at least 50% overall attendance and in each of the four blocks of the intervention, in addition to being duly evaluated in the line moments baseline and post-intervention. This decision aligns with the intervention proposal, in which the initial meetings comprised more theoretical activities, with practical sessions beginning in the second month onwards. Those from the GC who participated in the assessments will also be considered. The second analysis will include all individuals from the CG who participated in both data collections, and those from the IG considered in the per-protocol analyses. To fill in the missing data from the other participants, the multiple imputation technique will be applied, using sex, age, and the variables of interest as predictors. For comparisons between periods (pre- and post-intervention) and between groups (intervention and control), analysis will be conducted using generalized estimating equations (GEE), with Bonferroni post hoc adjustments. The significance threshold will be set at *p* ≤ 0.05. However, for time*group interactions, *p* ≤ 0.10 will be considered marginally significant [126]. Additionally, effect sizes will be calculated based on (a) Cohen’s d [127], considering small values (0.20 ≤ d < 0.50), medium values (0.50 ≤ d < 0.80), and large (d ≥ 0.80); and (b) partial eta squared (ηp2), with small (0.02 ≤ ηp2 < 0.13), medium (0.13 ≤ ηp2 < 0.26), and large (ηp2 ≥ 0.26) effect sizes [128]. These procedures will be performed using the Statistical Package for the Social Sciences (SPSS, version 23.0) software.

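### The intention-to-treat analysis draws its intervention data only from the per-protocol set, and its stated imputation predictors name neither randomised group nor attendance; the direction of the bias depends on the unstated group term

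*Protocol article*

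**What the plan says.** All of this is in the protocol article, mainly under Data treatment and statistical analyses.

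- **Per-protocol rule.** Intervention participants count if they stayed to the last meeting, "with at least 50% overall attendance and in each of the four blocks of the intervention", and were assessed at baseline and post-intervention. The programme has 32 meetings in four blocks of eight, so the floor is 4 of 8 in every block and 16 of 32 overall.
- **Intention-to-treat analysis.** "The second analysis will include all individuals from the CG who participated in both data collections, and those from the IG considered in the per-protocol" set.
- **Imputation.** Its purpose is given as "To fill in the missing data from the other participants". On the method and its inputs, the article says that "the multiple imputation technique will be applied, using sex, age, and the variables of interest as predictors".
- **Meaning of the last predictor.** Under Assessments the same phrase denotes what was measured at the visits: "The assessment of the variables of interest was carried out at three moments". Neither attendance nor allocation is a measure of that kind.
- **Expected loss.** Under Sample size, randomization, and allocation concealment: "Anticipating a potential dropout rate of up to 50" per cent.

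**The concern.** The set described as intention-to-treat is the per-protocol set with imputed values added. Every intervention participant whose outcome feeds the imputation attended at least half of each block. As worded, a low attender who came to the May visit is among those to be filled in, although the outcome was observed.

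Multiple imputation is credible only if the model contains what predicts both missingness and outcome. Two candidates are absent from the stated list. One is randomised group, without which an effect of treatment cannot carry into the imputed values. The other is attendance, which the trial must hold because its per-protocol rule needs it. With dropout of up to half anticipated, imputed values could make up a large share of the primary outcome, so this choice can move the headline estimate.

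**Working it through.** **1. The plan's own figure.** For the time-by-group term of a repeated-measures ANOVA, lambda = f² × N × m / (1 - rho) = 0.25² × 28 × 3 / 0.5 = 10.5, with 2 and 52 degrees of freedom. The correlation of 0.5 and sphericity are assumed, as the article states neither. Power is 0.812, so 28 reproduces, and 28 / (1 - 0.5) = 56. The sample size is not at issue. It shows only how much weight imputation may carry.

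**2. Direction of bias, by algebra, with the donors as written.** Let the effect in adherers be 1, let theta be the share of it that intervention leavers keep, and let dI and dC be the shares to be imputed in each arm. Assume that control leavers resemble control stayers.

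- True effect = (1 - dI) + dI × theta
- Group in the model: estimate = 1
- Group absent: p = (1 - dI) / [(1 - dI) + (1 - dC)] is the share of donors from the intervention arm, and estimate = (1 - dI) + dI × p - dC × p

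Example with dI = 0.5 and dC = 0: p = 0.5 / 1.5 = 0.333, and the estimate is 0.5 + 0.5 × 0.333 = 0.667.

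| dI / dC | theta | True | Bias with group | Bias without group |
|---|---|---|---|---|
| 0.5 / 0.5 | 0 | 0.50 | +0.50 | 0 |
| 0.5 / 0.5 | 0.5 | 0.75 | +0.25 | -0.25 |
| 0.5 / 0.5 | 1 | 1.00 | 0 | -0.50 |
| 0.5 / 0 | 0 | 0.50 | +0.50 | +0.167 |
| 0.5 / 0 | 0.5 | 0.75 | +0.25 | -0.083 |
| 0.5 / 0 | 1 | 1.00 | 0 | -0.333 |
| 0.3 / 0.3 | 0 | 0.70 | +0.30 | 0 |
| 0.3 / 0.3 | 0.5 | 0.85 | +0.15 | -0.15 |
| 0.3 / 0.3 | 1 | 1.00 | 0 | -0.30 |

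A simulation (56 participants, 1,500 trials, adherer effect -3 points) agrees. At 0.5 / 0.5 and theta = 0.5, the true effect is -2.29; the estimate is -3.03 with group and -1.53 without.

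**3. If every observed May value is kept.** Assumed inputs: 28 per arm, PHQ-9 SD 5, baseline correlation 0.5, -6 points at full attendance, half of controls missing, and intervention values missing in 60-90% below half attendance and 10-30% above. Estimates in PHQ-9 points:

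| Benefit by attendance | True | By arm, no attendance | By arm, with attendance |
|---|---|---|---|
| Proportional | -3.1 | -3.6 to -4.4 | -3.1 to -3.2 |
| Diminishing returns | -4.1 | -4.5 to -4.8 | -4.1 to -4.2 |
| Threshold at 50% | -3.2 | -4.1 to -5.0 | -3.4 to -4.0 |
| Unrelated | -3.0 | -2.9 | -2.9 |

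- Proportional: 3.6 / 3.1 = 1.16 and 4.4 / 3.1 = 1.42.
- Threshold: 4.1 / 3.2 = 1.28 and 5.0 / 3.2 = 1.56. These rows cover 60-80% loss among low attenders. At 90% loss the overstatement reaches about 70%, and even with attendance the estimate is -4.6.
- Diminishing returns: 4.5 / 4.1 = 1.10 and 4.8 / 4.1 = 1.17.
- Group left out, proportional benefit: -1.8 to -2.1 against -3.1, an understatement of 32-42%.

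**4. Attendance added to the plan as it stands.** With per-protocol donors only, no donor lies below 50% attendance, so the model extrapolates. With 50% leavers who gain nothing (true effect about -1.5), the estimate goes from -2.97 to -3.00 and its SD from 1.49 to 2.59. With the threshold effect of step 3 (true -3.2), it stays near -5.9 and the SD rises from about 1.9 to 3.3.

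**The case against.** A reader might infer that leaving attendance out causes early leavers to be treated as full participants, so that the effect is overstated. The documents do not support that. It requires group in the imputation model, and the stated list does not name group. Read literally, the list biases mostly towards no effect. The article also does not report how leavers fared or how many lacked a May PHQ-9.

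A second tempting reading is that attendance is the strongest known link between leaving and outcome. The Introduction says only that symptoms bring low motivation and loss of interest, "common factors for discontinuation of health promotion efforts across various contexts". It does not say that attendance predicts the May score.

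Three further objections carry weight:

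- A linear attendance term looks best when the true effect is linear. Under a threshold it removes only about 40-70% of the bias.
- Perhaps 1 to 5 low attenders would have a May value to set the slope. Under the proportional scenario, RMSE without and with attendance was 1.84 and 1.84, 1.93 and 1.97, and 2.10 and 2.35: no gain.
- A journal article may leave auxiliary variables to a fuller plan. That excuses silence, but this article states both the set and the predictors, and the set is wrong for its label whatever a fuller plan adds.

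Two kinder readings remain open: that group is meant among the variables of interest, and that observed May values outside the per-protocol set are kept. The text says neither. Together they lead to step 3, where the estimate is still overstated if benefit depends on attendance.

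**Conclusion.** The point holds in this form: the intention-to-treat set is built on the per-protocol intervention group, and the stated imputation predictors name neither group nor attendance. The sign of the bias is not fixed by the text. Without group the effect tends to be understated (by about a third or more under proportional benefit), although the bias can be zero, or upward when only the intervention arm loses people who gained nothing. With group or by arm it is overstated whenever leavers benefit less: about 15-70% in the proportional and threshold scenarios and 10-17% under diminishing returns, even with all observed outcomes used. It is zero if benefit does not depend on attendance.

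All sizes rest on assumed SD, correlation, effect and missingness, because the article gives none of these beyond the dropout ceiling. The faults in the donor set and the missing group term are the primary ones. Attendance is a useful refinement once those are repaired, and adding it alone does not reliably help.

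**What to change.** Under Data treatment and statistical analyses, redefine the intention-to-treat analysis in four parts:

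1. Include all randomised participants in their allocated group.
2. Keep every observed May PHQ-9, whatever the attendance; impute only what was not observed.
3. Impute separately by arm from baseline PHQ-9, sex and age; in the intervention arm add the number of meetings attended as an auxiliary predictor.
4. Add a sensitivity analysis in which intervention leavers are imputed from the control arm, or with a stated delta adjustment. Few low attenders may have May data, and attendance cannot remove all of the bias.

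The cost is a few sentences and one variable already on file. The interval widens: the SD of the estimate rises by roughly 3-40% in simulation, with little or no gain in RMSE at 28 per arm. The benefit is less bias and an analysis that matches its label. Parts 1 to 3 belong together. The trial is reported as concluded, so the change should be dated, and labelled as made after the data were seen if that is the case.

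### The primary GEE test runs on about 28 completers (56 at most) with no small-sample correction stated; without one, the nominal 5% level becomes about 6% to 7%

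*Protocol article*

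**What the plan says.** Under *Sample size, randomization, and allocation concealment*, the calculation "was based on an ANOVA model for repeated measures with three time points and two groups", with effect size 0.25 and "statistical power of 80%, and 5% significance level for two-tailed tests, reaching a value of 28 individuals". It continues: "Anticipating a potential dropout rate of up to 50%, the number calculated was doubled, bringing the total sample size to 56 individuals". Allocation is 1:1.

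Under *Data treatment and statistical analyses*, the method changes. For the pre/post and between-group comparisons, "analysis will be conducted using generalized estimating equations (GEE), with Bonferroni post hoc adjustments", and the software is SPSS 23.0. The threshold is p ≤ 0.05, and a time-by-group interaction at p ≤ 0.10 is to be called marginal.

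Two analysis sets are planned:
- A per-protocol set. Intervention participants must stay to the end and attend at least half the sessions overall and within every block. Controls need only be assessed.
- A set labelled intention-to-treat, in which the remaining participants are filled in by multiple imputation. Its size can approach 56.

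The article names no covariance estimator, working correlation, reference distribution or finite-sample correction.

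**The concern.** The sample size rests on a repeated-measures ANOVA, whose F reference allows for limited degrees of freedom. The analysis uses GEE. Its sandwich variance is biased downward when there are few participants, and its normal or chi-square reference is too narrow. The 5% level used in planning therefore belongs to a different test from the one that will be run.

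At stake is the error rate of the primary efficacy test and the coverage of its confidence interval. The 10% rule for the interaction adds to this, because it already invites weak results to be read as signals and would be inflated too.

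**Working it through.** **1. The plan's own figure.** Inputs from the sample-size section: f = 0.25, m = 3 time points, k = 2 groups, α = 0.05, power 80%. Correlation 0.5 and sphericity are assumed, since the article gives neither. For the within-between interaction, λ = f²·N·m/(1 − ρ) = 0.0625 × 28 × 3/0.5 = 10.5, with (k − 1)(m − 1) = 2 and (N − k)(m − 1) = 52 degrees of freedom. The power is 0.812, so N = 28 is reproduced. Then 28/(1 − 0.5) = 56. Balanced analysis sizes therefore run from 14 v 14 to 28 v 28.

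**2. Type I error, balanced arms.** With two time points, complete data and a saturated mean model, the GEE interaction is the difference in mean change between arms. With n per arm, the uncorrected sandwich divides by n rather than n − 1, so its variance is (n − 1)/n times the unbiased pooled one. For normal data the test rejects when a t statistic on 2n − 2 degrees of freedom exceeds z·√((n − 1)/n).

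- n = 14: 1.960 × √(13/14) = 1.889, and P(|t₂₆| > 1.889) = 7.0%.
- n = 28: 1.960 × √(27/28) = 1.925, and P(|t₅₄| > 1.925) = 5.9%.
- At nominal 10%: cut-offs 1.585 and 1.615 give 12.5% and 11.2%.
- Pooled model-based standard error with z: P(|t₂₆| > 1.960) = 6.1% and P(|t₅₄| > 1.960) = 5.5%.
- Pooled standard error with a t reference: 5.0% in both.

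Simulation with 200,000 trials per setting agrees: 7.1% and 5.9% for the sandwich, 6.1% and 5.4% for the model-based form.

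**3. Interval width.** The ratio of the uncorrected to the corrected interval is 1.960·√((n − 1)/n)/t₀.₉₇₅. For n = 14 this is 1.889/2.056 = 0.919, about 8% too narrow. For n = 28 it is 1.925/2.005 = 0.960, about 4% too narrow.

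**4. Check with fitted models.** Exchangeable GEE fits (3,000 trials each, Monte Carlo standard error about 0.5 points), at N = 28 and N = 56:

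| Variance and reference | N = 28 | N = 56 |
|---|---|---|
| Sandwich, z | 6.9% | 6.5% |
| Model-based, z | 7.4% | 6.6% |
| Bias-reduced sandwich, z | 5.1% | 5.4% |
| Bias-reduced sandwich, t on N − 2 | 4.3% | 5.1% |

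The fitted model-based rates are above the pooled figures in step 2, so 6.1% and 5.5% should not be read as an upper limit for that option.

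**5. Unequal arms (assumed splits).** The article gives no analysed counts by arm. For illustration, the sandwich with z gives 7.6% at 10 v 20 and 8.4% at 8 v 20 (13.2% and 14.2% at nominal 10%). The pooled model-based form stays near 6% in both.

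**The case against.** The strongest reply is that the point rests on silence. A journal article condenses a fuller document, and a variance estimator with its correction is a detail often left there. That limits the claim: the article does not specify an uncorrected estimator, so nobody can say that the p-values will be wrong, only that they would be unless a correction is applied. It does not remove the point. The article itself commits to a large-sample method for a sample this small, and both usual uncorrected forms exceed 5%.

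A reader might also infer larger errors, of roughly 9% to 12%. Rates of that order arise for a two-degree-of-freedom interaction over three time points with small or unequal arms. The GEE comparison that the article describes is pre versus post. Three time points appear in the sample-size model and the assessment schedule, not in that comparison, so those rates are not evidence about the stated test.

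Nor do the documents show that the arms will be unequal in a particular direction. The attendance rule trims only the intervention arm, but the section on experimental procedure also expects control participants to drop out. The splits in step 5 are illustrations.

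Finally, 28 is the number left at the maximum dropout allowed for, and the imputed set may approach 56, where the sandwich excess is under one percentage point in the closed form. That stands and keeps the severity down. Equally, 28 is not a floor for the per-protocol set, which the attendance rule could make smaller.

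**Conclusion.** The point holds in conditional form, at low to moderate severity. Unless a small-sample correction is applied, the primary pre/post interaction test at nominal 5% has a type I error of about 7% (14 v 14) or 6% (28 v 28) with the sandwich, and about 6% or 5.5% with a pooled model-based standard error. With 14 per arm and the sandwich, roughly 1 null trial in 14 would be declared significant instead of 1 in 20. The 10% threshold becomes about 12.5% or 11%. Unequal arms would raise the sandwich rate further, to 7.6% or 8.4% at the assumed splits.

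The figures rest on normal errors, equal variances and complete data. The imputation step is not modelled, and the sandwich is an assumption because the article names no estimator. The documents do not support the stronger statement that the planned p-values are known to be invalid.

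**What to change.** In *Data treatment and statistical analyses*, state that the GEE uses a bias-corrected sandwich (such as Mancl-DeRouen or Kauermann-Carroll) with a t or F reference. Name the working correlation and the degrees of freedom in the same sentence. The reference distribution matters as much as the variance: in step 2, an unbiased variance with z still gives 6.1% at 14 v 14. A linear mixed model with Kenward-Roger degrees of freedom is an acceptable alternative.

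The cost is small. This model moves from SPSS to R, which the plan already names, and intervals widen by about 9% at N = 28 (1/0.919) or 4% at N = 56 (1/0.960) relative to the uncorrected sandwich. Some corrections are slightly conservative at the smallest size, as the 4.3% in step 4 shows. The trial has concluded but the analyses are described in the future tense. If they have already been run, the corrected results can be reported beside them.

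### The time-by-group interaction, which is the efficacy test, has its own p ≤ 0.10 tier labelled marginally significant, although the trial was sized at two-sided 5%

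*Protocol article*

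**What the plan says.** The section on data treatment and statistical analyses describes how the intervention effect on the primary and secondary outcomes will be assessed, in both per-protocol and intention-to-treat analyses. Pre- and post-intervention values are compared between intervention and control by GEE with Bonferroni post hoc adjustment. The general threshold is p ≤ 0.05. The next sentence singles out one term: "However, for time*group interactions, *p* ≤ 0.10 will be considered marginally significant". It cites a source for this and does not restrict it to secondary or exploratory outcomes.

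The section on sample size uses a different standard. The calculation "was based on an ANOVA model for repeated measures with three time points and two groups", with "statistical power of 80%, and 5% significance level for two-tailed tests, reaching a value of 28 individuals". The section on study variables names depressive symptoms as the primary outcome.

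**The concern.** In a model with period, group and their interaction, the period main effect does not compare the arms, and the group main effect does not measure a difference in change. Only the interaction estimates how much more one arm changed than the other. A looser threshold is sometimes tolerated for interactions that screen for effect modification. Here the interaction is the efficacy test itself.

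The extra tier is thus attached to the one term on which the trial's main conclusion depends, at twice the error rate assumed in the sizing. The protocol does not say that a marginal result will not support a claim of effect. The same tier is available for each secondary outcome and in both analysis sets.

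**Working it through.** **Inputs from the protocol.** Two-tailed alpha 0.05; power 80%; effect size 0.25; two groups and three time points; 1:1 allocation; total 28, doubled to 56 for dropout of up to 50%; analysis threshold p ≤ 0.05; interaction tier p ≤ 0.10.

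**Assumptions not in the protocol.** The effect size is read as Cohen's f. The correlation between repeated measures is ρ = 0.5 and the sphericity factor is ε = 1, taken as software defaults.

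**1. Reproduce the plan's figure.** For the within-between interaction with k = 2 groups and m = 3 times:

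- λ = f²·N·m/(1 − ρ) = 0.0625 × 28 × 3 / 0.5 = 10.5
- df1 = (k − 1)(m − 1) = 2
- df2 = (N − k)(m − 1) = 26 × 2 = 52
- Power at alpha 0.05 = 0.812

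So N = 28 is reproduced, and 28/(1 − 0.5) = 56. The between-groups formula would need 86, so the stated number matches a time-related F test at alpha 0.05. With two groups the within-factor and interaction formulas give the same number, so the match alone does not prove that the interaction was meant. The match also depends on ρ: 0.3 gives 38 and 0.7 gives 18. The comparison of alpha levels does not depend on ρ.

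**2. The same calculation at alpha 0.10.** N = 22 suffices (λ = 8.25, df2 = 40, power 0.804), or 44 after doubling. At N = 28 the power is 0.889. The 0.10 tier is therefore a different error standard from the one behind the stated 28.

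**3. Size of the marginal band under the null.** With a correctly calibrated test, P(0.05 < p ≤ 0.10) = 0.10 − 0.05 = 0.05. A simulation of 100,000 null trials comparing change between two arms by t-test agrees:

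| Per arm | p ≤ 0.05 | p ≤ 0.10 | Between |
|---|---|---|---|
| 14 | 0.050 | 0.100 | 0.050 |
| 28 | 0.050 | 0.100 | 0.050 |

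**4. A separate matter: small-sample calibration of the GEE test.** The protocol names GEE but not the variance estimator. Suppose an uncorrected robust Wald chi-square is used. With n per arm and two time points, the statistic is the two-sample t on change multiplied by √(n/(n − 1)), referred to the normal distribution. The true rate is then P(|t| > z·√((n − 1)/n)) on 2n − 2 degrees of freedom.

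| Per arm | Cut-off at 0.05 | Rate | Cut-off at 0.10 | Rate |
|---|---|---|---|---|
| 14 (df 26) | 1.889 | 7.0% | 1.585 | 12.5% |
| 28 (df 54) | 1.925 | 6.0% | 1.615 | 11.2% |

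Fourteen per arm is the worst case, with the full 50% dropout; 28 per arm is no dropout. The excess over nominal comes from the assumed estimator, is present at 0.05 as well, and would not be removed by deleting the tier.

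**The case against.** The strongest reply is that the protocol does not replace 0.05 with 0.10. It states the 0.05 threshold first, and marginally significant names something weaker than significant. A reader might infer that efficacy will be declared at p ≤ 0.10 and that the primary type I error is therefore 10%. The text does not say so: at the stated threshold the nominal rate of a significant result is still 5%. That part of the reply stands, and the doubling is conditional on how the label is used.

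A reader might also attribute the 12.5% figure to this sentence. That is not supported. Part of it is small-sample inflation that depends on an unstated estimator and on worst-case dropout.

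A third inference is that a marginal interaction will lead to within-arm pre/post changes being presented as proof of effect. The protocol plans Bonferroni post hoc comparisons but does not say this, so it remains a prediction.

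The tier is also openly declared and referenced, so readers can apply 0.05 themselves. The cited source cannot be examined here. But declaring a second tier does not reconcile it with the 5% used for sizing. Nor is this a detail left to a fuller plan, because the rule is stated in the article.

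**Conclusion.** The point holds in a limited form. The protocol gives a special p ≤ 0.10 label to the term that tests the intervention effect, including on PHQ-9, while sizing the trial at two-sided 5%. About 5% of null trials would receive that label in addition to the 5% called significant. If the label is taken as evidence of an effect, the nominal false-positive rate per test is 10%.

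That figure assumes a correctly calibrated test. That the interaction is the efficacy test follows from the pre/post by group model, since the protocol does not name it as such. The formal threshold, the model and the sample size are not affected. The appropriate grade is should-fix.

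**What to change.** Delete the sentence that creates the 0.10 tier. State that the time-by-group term for PHQ-9 is judged at two-sided 0.05, and report the between-group difference in change with its 95% confidence interval, which conveys the strength of evidence better than a second label.

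This changes one sentence and needs no added sample: 28 still gives power 0.81 at alpha 0.05 under the assumptions above. The cost is that a result with p between 0.05 and 0.10 is reported as not significant. Data collection has ended, but the analyses are written in the future tense, so the reporting rule can still be corrected. The choice of GEE variance estimator should be dealt with separately.
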